##### Handling of missing data and drop-outs

Since the number of clusters may depend on the number of tests per each class, we will collect information on the number of students who agreed to be enrolled in each class, each week, and we will take into consideration this information in the statistical analysis, adjusting and stratifying for the response rates.

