### Study outcomes

#### Cluster randomised interventional study

##### Primary outcomes

Frequencies of clusters in classrooms in which pooled saliva tests (LM) are performed in association with standard contact tracing protocols, compared with classrooms in which SoC only protocols are applied.Number of classes and of students in the classes that accept to participate in the LM study, if asked, during time.

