#### Exclusion criteria

No informed consent by schools or children, or the adult participant.Suspicion of acute COVID-19 infection:
In case of unknown respiratory infection, no presence of symptoms that can be attributed to SARS-CoV-2 for at least 48 h.In case of confirmed SARS-CoV-2 infection: exclusion for at least 21 days from PCR-positive diagnosis and no presence of symptoms for at least 48 h.

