##### Control intervention

The classes in the control group, including the assigned teachers and school personnel, will follow SoC countries measures regarding surveillance based on symptoms and contact tracing. The usual surveillance will be conducted by the personnel devoted to it in SoC situation. Study personnel from the involved PIs will be available to support.

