#### Procedures at each visit

The Lolli will be performed two days a week, the “Lolli days”. The procedure can be managed autonomously by the schools or with support by an external person from the research centre.

Each Lolli day, the students who participate in the trial are given a swab at the entrance in class. They suck the swab for 30 s and then they all enter their swabs into the same large tube for the class. The teacher and the non-teaching personnel do the same.

The teacher puts a label with the class ID and barcode on the tube and enters into the eCRF the information of questionnaire T1 (date, class identifier, n. of absent pupils, n. of pupils who refused to carry out the test).

The responsible person for each school collects the tubes and puts them into a plastic bag.

The contracted courier authorised to biological samples transportation will then arrive at agreed time and will bring the plastic bag containing all the tubes to the laboratory. Tubes will be sent to the study laboratory in the morning. Results will be returned to the monitor in the same day.

If the pool is positive, the monitor will contact the school and the Public Health authorities in the same day and request the positive class participants to return to school the day after to collect the Lolli test for the individual testing. While waiting for the individual results, the tested participants will return back home or go to school according to the national regulation in force.

The individual results will then be communicated to the relevant public health authorities who will conduct the epidemiological investigation supported by the study questionnaire and will assign the containment measures according to the regulation in force.

The procedures set in place to accomplish the objectives of this project will be monitored during the entirety of the study by the PIs of the centre that enrolled the school.

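### Adjusting or stratifying the LM versus SoC comparison for weekly response rates would condition on a post-randomisation variable and can bias the LM effect in either direction

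*Protocol article*

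**What the plan says.** The Protocol article, under Handling of missing data and drop-outs, gives its motive first: "Since the number of clusters may depend on the number of tests per each class". It continues "we will collect information on the number of students who agreed to be enrolled in each class, each week" and concludes "we will take into consideration this information in the statistical analysis, adjusting and stratifying for the response rates". It does not name the model or the contrast that carries this adjustment, and it does not limit it to a baseline value, a sensitivity analysis or one arm.

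Other sections bear on what this variable is:

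- **Procedures at each visit.** On each Lolli day the teacher enters questionnaire T1, which holds "date, class identifier, n. of absent pupils, n. of pupils who refused to carry out the test". This is the only weekly participation record the article describes.
- **Control intervention.** SoC classes "will follow SoC countries measures regarding surveillance based on symptoms and contact tracing". They have no Lolli sessions.
- **Primary outcomes** of the interventional study include "Number of classes and of students in the classes that accept to participate in the LM study, if asked, during time". Participation per class over time appears again among the secondary outcomes.
- **Exclusion criteria.** A confirmed infection leads to "exclusion for at least 21 days from PCR-positive diagnosis and no presence of symptoms for at least 48 h". Recruitment and screening says that these criteria are checked at the start of every testing session.
- **Primary analysis (LM evaluation trial).** Cluster frequencies are compared between arms with an unadjusted chi-square or Fisher test.

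**The concern.** Randomisation protects a comparison of classes by assigned arm. It does not protect a comparison made within levels of something that happens afterwards and that both the arm and the outcome can change. Weekly response appears to be such a variable. Invitations to be sampled twice a week exist only in LM classes, and infections can remove pupils from the sessions. If it enters an LM versus SoC model as a covariate or stratum, the LM coefficient no longer estimates the effect of assignment.

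The motive is sound, since more testing finds more clusters. But the main imbalance in testing lies between the arms: scheduled pooled PCR plus usual surveillance on one side, usual surveillance alone on the other. A participation rate cannot supply the infections that symptom-prompted testing and contact tracing did not find. The adjustment therefore adds a risk of bias without solving the problem it is meant to solve.

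**Working it through.** The plan gives no figure for this adjustment, so the check is mainly one of structure.

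**1. Timing.** The count is repeated weekly over a six-month intervention, so it is measured after randomisation.

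**2. Dependence on arm.** T1 is completed on Lolli days, and only LM classes have them. An LM versus SoC model that needs a weekly response in every class must therefore assign SoC classes a value that the article does not define.

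**3. Dependence on outcome.** The plan's 8,800 people in 440 classes give 8,800 / 440 = 20 per class. A cluster is at least two cases in a school week. If excluded cases count as non-response and everyone else takes part, two cases lower response by 2/20 = 10 percentage points. An exclusion of at least 21 days covers about three school weeks, or 3 × 2 = 6 sessions.

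**4. Status as outcome.** Participation over time is listed as an effect to be measured. It is then also proposed as a covariate.

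**5. Possible size, for illustration only.** All inputs here are assumptions apart from the class size and the roughly 4% cluster rate: 24 weeks, 20 pupils per class, about 4% weekly cluster risk varying between classes, cases out for three weeks starting in the week of the cluster. There were 2,200 classes per arm and one run per scenario. A logistic model of weekly cluster on arm was fitted without and with weekly response.

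| Scenario | OR without response | OR with response |
|---|---|---|
| No LM effect; case exclusion equal in both arms | 1.01 | 0.97 |
| No LM effect; participation falls 20 points in LM, unrelated to cases or risk | 0.98 | 0.93 |
| No LM effect; no case exclusion; 20-point fall plus risk-linked refusal in LM | 0.93 | 0.52 |
| No LM effect; case exclusion plus 20-point fall in LM | 0.98 | 0.09 |
| True risk ratio 0.5; case exclusion only | 0.49 | 0.72 |
| True risk ratio 0.5; case exclusion plus 20-point fall in LM | 0.51 | 0.05 |

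The estimate without response stays near the truth throughout. With response it moves towards no effect in one scenario and far away from it in others.

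A second set used the trial's own size (220 classes per arm), no LM effect, and LM response of 85% with an SD of 8 points. It shows how much the coding of SoC matters:

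- **SoC held constant at 85%, LM response falling in the cluster week.** The adjusted OR is about 0.81 for a 5-point fall (about half of trials falsely significant) and about 0.45 for a 10-point fall (virtually all).
- **Both arms falling equally.** OR about 1.00, with 5–7% rejected.
- **LM fall delayed to the following week.** OR 0.99, with 5–6% rejected.

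**6. Effect of the fix on sample size.** The plan's calculation is for an unadjusted comparison of proportions. With 4% versus 0.5% (4% minus the stated 3.5% difference), one-sided 5%, 80% power and pooled variance:

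n = [1.645·√(2·0.0225·0.9775) + 0.842·√(0.04·0.96 + 0.005·0.995)]² / 0.035² ≈ 221 per arm.

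This matches the stated 220. The calculation relies on no response adjustment, so omitting it changes nothing.

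**The case against.** The strongest reply is that the primary comparison is unadjusted. The section on missing data names no model, and multivariable cluster models appear only under the heading for the ancillary observational study. A condensed article may leave the model to a fuller document. This stands in part. A reader might infer that the randomised comparison is lost, but the documents do not support that, because the unadjusted contrast remains in the plan. What remains is a stated rule, motivated by the main endpoint and not confined to the observational study, which an analysis plan could carry into the arm comparison.

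Second, the covariate is worded as agreement to enrol, and T1 keeps absences apart from refusals. A pupil at home with an infection has not withdrawn agreement, so cases need not lower the rate. This is a fair reading. The article does not name T1 as the source, and that link is an inference. The stated motive, however, is the number of tests, which cases excluded at sessions do reduce.

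Third, if SoC classes have no weekly response, perhaps only stratification within the LM arm is meant. That would be harmless to the arm contrast, but the text does not say so.

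Two further inferences should be avoided. SoC classes are not untested, since they are tested on symptoms and through contact tracing. Nor does the article fix that exposed classmates stay home: those who test negative may return, and the rule while results are awaited follows national regulation.

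**Conclusion.** The concern holds as a risk created by a stated rule. If weekly response is used in an LM versus SoC comparison, it can bias the LM effect in either direction, and it cannot remove the built-in difference in testing between arms. The unadjusted primary comparison is unaffected.

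A reader might take the odds ratios of 0.81 and 0.45 as the expected bias. They are one illustrative scenario, resting on a constant SoC value and a fall in LM response in the same week as the cluster. The distortion disappears when both arms fall equally or the fall is delayed. Neither the size nor the direction can be derived from the documents.

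The conclusion rests on two readings: that the rule is meant to reach the arm comparison, and that response can change with arm, cases or both. If participation were unrelated to cases and risk, the bias would be small. The point should be corrected, but it does not invalidate the main analysis.

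**What to change.** In Handling of missing data and drop-outs, state that:

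1. The LM versus SoC comparison includes all randomised classes by assigned arm and is not adjusted or stratified for response measured after randomisation.
2. Any adjustment of that comparison uses only values fixed before randomisation: class size, number of consented members, and the age stratum used in the randomisation.
3. Weekly response is reported descriptively, or used only in a labelled exploratory analysis within the LM arm that relates clusters to response in earlier weeks.

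The section should also define the response rate, including its denominator and whether absent or excluded pupils count as non-responders, and name its data source.

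The cost is protocol and analysis plan wording. The number of classes, the power calculation and the data collection stay as they are.

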## Discussion

The EuCARE consortium involves 18 partners from 10 different countries and has been funded by the European Commission in the frame of the research aimed at fighting SARS-CoV2 virus and its variants, in the context of the EuCARE project, “European Cohorts of Patients and Schools to Advance Response to Epidemics”. The project’s ultimate goal is to find solutions to safely support school reopening within the COVID-19 pandemic on the basis of scientific evidence, taking in consideration the impact that a prolonged school closure can have on education, wellbeing and personal development of children.

As detailed in the website (https://eucareresearch.eu/studi-sulle-scuole), the study -which involves a multidisciplinary group of scientists- is made of two parallel sub-studies: an observational and an interventional study, to evaluate epidemiological and psychological aspects, prevention measures and efficacy of the saliva-based “Lolli-Methode” for COVID-19 screening. The “Lolli-Methode” is based on the collection of saliva samples from students, teachers and school personnel, which are pooled and analyzed together by PCR, making this screening approach quick and cheap. In case of a positive result, samples are re-collected and re-analyzed individually.

In the frame of this project, a pilot study has been already conducted, demonstrating the feasibility and reliability of the method, and in September 2022 the whole study will be launched, which will involve schools in Portugal, Germany, Mexico and Italy, for a total of 440 kindergarten, elementary, intermediate and high school classes.

In this context, we have recently published the results of a meta-analysis [10] showing that students play a significantly minor role in viral spread as compared to teachers. Our analysis is based on SARS-CoV2 infections data from 22 studies, involving over 120.000 subjects including students, teachers and other personnel, from Europe, United States and Israel, and considered results of screenings, contact tracing, and antibody presence. We showed that schools did not increase transmission of COVID-19 but mirrored the infection spread within the community. Moreover, students resulted to be less susceptible to infection and less infective, as infections most frequently occurred between teacher and student.

By the end of this study, we will have identified and characterised the applicability of the LM for SARS-CoV-2 surveillance, as well as the impact of pandemic preventive measures on children.

## Data Availability

Data sharing is not applicable to this article as no datasets were generated or analysed during the current study.

## Abbreviations

AI: Artificail intelligence
LM: Lolli-Methode
NPI: Non-pharmacological intervention
SoC: Standard of care
VoC: Variant of concern
